## Abstract

Atherosclerotic Cardiovascular Disease (ASCVD) represents the leading cause of death worldwide, and individual screening should be based on behavioral, metabolic, and genetic profile derived from data collected in large population-based studies. Due to the polygenic nature of ASCVD, we aimed to assess the association of genomics with ASCVD risk and its impact on the occurrence of acute myocardial infarction, stroke, or peripheral artery thrombotic-ischemic events at population level. CardioVascular Genes (CV-GENES) is a nationwide, multicenter, 1:1 case-control study of 3,734 patients in Brazil. Inclusion criterion for cases is the first occurrence of one of the ASCVD events. Individuals without known ASCVD will be eligible as controls. A core lab will perform the genetic analyses through low-pass whole genome sequencing and whole exome sequencing. In order to estimate the independent association between genetic polymorphisms and ASCVD, a polygenic risk score (PRS) will be built through a hybrid approach including effect size of each Single Nucleotide Polymorphism (SNP), number of effect alleles observed, sample ploidy, total number of SNPs included in the PRS, and number of non-missing SNPs in the sample. In addition, the presence of pathogenic or likely pathogenic variants will be screened in 8 genes (*ABCG5*, *ABCG8*, *APOB*, *APOE*, *LDLR*, *LDLRAP1*, *LIPA*, *PCSK9*) associated with atherosclerosis. Multiple logistic regression will be applied to estimate adjusted odds ratios (OR) and 95% confidence intervals (CI), and population attributable risks will be calculated.

**Clinical trial registration:** This study is registered in clinicaltrials.gov (NCT05515653).

## Introduction

Atherosclerotic cardiovascular disease (ASCVD) represents the leading cause of death worldwide. Overall, one third of deaths is due to cardiovascular disease [1, 2]. Assessment of consistency or variability in the associations between risk factors and cardiovascular disease (CVD) and mortality, both globally and in countries grouped by income levels, will help the development of global and local strategies for prevention. International cohort findings indicate that over 70% of CVD can be attributed to a small cluster of modifiable risk factors [3].

Low-and middle-income countries are substantially affected by CVD. In Brazil, these conditions are responsible for more than 300,000 deaths/year, representing the main cause of death, followed by cancer, respiratory diseases, and diabetes. Collectively, chronic non-communicable diseases (NCDs) are responsible for approximately 70% of the causes of death in both sexes [1, 2, 4, 5].

Contemporary studies have shown that seven out of ten cases of CVD can be explained by modifiable risk factors such as hypertension, low level of education, smoking, dyslipidemia, unhealthy diet, abdominal obesity, sedentary lifestyle, diabetes, psychosocial factors, and air pollution [3]. Furthermore, advances in genetic sequencing technologies and greater access to them have led to the identification of genetic polymorphisms associated with increased risk of CVD, emphasizing the model of interaction between genetic background (non-modifiable) and environment (modifiable) as one of the triggers for CVD [6, 7].

The Brazilian population is unique due to its ethnic diversity, which may be relevant in the assessment of genomics impact on the risk of specific diseases, including CVD [8, 9]. The clinical relevance of genomics in the Brazilian population has been reported in infectious, autoimmune, and hematological diseases, as well as in drug pharmacokinetics and in transplant allocation system.[7, 10–15].

From a public health system perspective, epidemiological features of cardiovascular health in developing countries have been described [16, 17], but there is still an urgent need for studies with geographic representation to allow both regional and ethnic diversity as essential elements to data acquisition and analysis of CVD risk. We designed the case-control study CardioVascular-Genes (CV-GENES) to determine the population attributable fraction estimates of genetic profile in the occurrence of acute myocardial infarction, stroke, or peripheral artery thrombotic-ischemic events, after adjustment for potentially modifiable CVD risk factors in Brazil [18, 19].

## Materials and methods

### Protocol report

CV-GENES protocol version 2.0/2022 was reported through an adaptation of the *Standard Protocol Items*: *Recommendations for Interventional Trials* (SPIRIT). Fig 1 shows the study schedule of participant enrollment and assessments. The SPIRIT checklist is reported in S1 File. Protocol in original language and its English-translated version is in S2 File.

**Fig 1 pone.0289439.g001:**
[figure not shown]
SPIRIT study schedule for participant enrollment and assessments.

### Study design

A multicenter observational case-control study will be conducted at 50 centers from all major geographic regions in the country to account for ethnical, cultural, and socioeconomic aspects.

### Eligibility criteria

Cases: All participants aged ≥18 years who are hospitalized due to the first occurrence of an acute myocardial infarction (AMI), stroke, or peripheral artery thrombotic event, presenting in the first 7 days from symptom onset will be screened (S3 File).

Eligible cases must have signs and/or symptoms compatible with the acute manifestation of ASCVD. Case definitions include diagnostic criteria based on national and international guidelines. Acute myocardial infarction is defined as: clinical presentation, electrocardiogram patterns (new pathological Q waves, and/or ST-segment elevation of 1 mm in ≥ 2 contiguous leads, or 2 mm from V1 to V3, or new left bundle branch block, or new changes in the ST-T segment, and cTnI or cTnT curve compatible with acute myocardial injury of ischemic nature (which is currently named a type 1 acute MI). Stroke is defined as clinical signs of rapid development of focal or global brain function disorder, lasting more than 24 hours, with no apparent cause other than that of vascular origin (does not include trauma, cancer, infection of the central nervous system), and Computed Tomography or Magnetic Ressonance Imaging with positive results. Peripheral artery thrombotic event is defined as clinical presentation (pain, burning sensation, absence of pulse, decreased local temperature, changes in color) and diagnostic tests (Doppler ultrasound, angiotomography, or arteriography) that show interruption of flow to the lower limbs acutely, of embolic or thrombotic cause, leading to distal ischemia [20–23].

Controls: All participants aged ≥18 years seeking medical care for non-ASCVD conditions will be screened and enrolled during hospitalization; and healthy individuals with no clinical complain will also be screened and enrolled at the same community. Cases and controls will be recruited in a 1:1 ratio adjusted for sex and age.

Exclusion criteria for both cases and controls are previously known ASCVD, e.g., chronic coronary artery disease, stable angina, previous myocardial infarction, percutaneous revascularization procedures (coronary, cerebrovascular, or peripheral), surgical revascularization procedures in any arterial vascular bed, transient ischemic attack, stroke, aortic aneurysm, intermittent claudication, peripheral artery disease that led to amputation.

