### Variables

The exposure to modifiable risk factors in combination with genomic data (polygenic risk score) in both cases and controls will be expressed as odds ratios (95% CI). Multiple logistic regression models will be built to adjust and determine the strength of association between demographic variables (sex, age, race), traditional risk factors (smoking, diabetes, hypertension, obesity, anxiety and depression, unhealthy diet, physical inactivity, alcohol consumption, and apolipoprotein B/A1 ratio [ApoB/ApoA1], and genetic data [PRS]. For each variable with a higher chance of CVD (significant OR), attributable risk estimate will be calculated for the genetic component (PRS) and other covariables. Fig 2 shows the Polygenic Risk Score flowchart.

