The INTERHEART study showed that genetic risk markers for the occurrence of AMI, identified through genome analysis, appear to be broadly associated with AMI in several different ethnic groups. However, the population attributable risk to these genetic factors is relatively small compared to that of modifiable risk factors. In the Latin American subgroup, the impact of the genetic risk score was PAR 0.86 95% CI 0.74–0.93 and PAR 0.12 95% CI 0.02–0.42, respectively, for modifiable and non-modifiable factors. However, as already mentioned, there are no data exclusively from Brazilian individuals with adequate statistical power and standardized data collection of traditional risk factors and, therefore, recommended for an integrated assessment of the PRS impact on the PAR for the occurrence of atherosclerotic events.

In a review of the main studies of susceptibility loci for coronary artery disease, including those from important consortia such as CARDIoGRAM, MIGen, WTCCC and Cardiogenics, deCODE, CARDIoGRAM, C4D and CARDIoGRAM + C4D [47], important contributions were derived from the identification of 60 loci, whose mechanism of action is related to serum levels of LDL-cholesterol, lipoprotein (a) and triglycerides, blood pressure, obesity, coagulation profile, changes in endothelial and smooth muscle cells of the vascular wall, migration mechanisms and cell adhesion, immune activation, inflammation, cell growth, differentiation and apoptosis, as well as extracellular matrix constituents and also some loci with unknown function.

Polymorphisms in genes associated with the regulation of calcium levels (CASR, CYP24A1, CARS, DGKD, DGKH/KIAA0564 and GATA3) [48] and metalloproteinases (MMP-3 and MMP-9) [49] were also associated with an increased risk of coronary artery disease and AMI. The list of polymorphisms associated with AMI progressively increases, and some authors have already reinforced the importance of using the genetic background in cardiovascular risk calculators [50–52].

Regarding stroke cases, polymorphisms in some genes such as MTHFR, eNOS, ACE, AGT, ApoE, PON1, PDE4D were associated with a higher risk of ischemic stroke. For cases of hemorrhagic stroke, polymorphisms in collagen genes, TLR4 and CD14 and even the gene that gives rise to C-reactive protein were identified [53].

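### Hospital controls may be admitted for illnesses caused by the exposures under study, which can bias those factors' odds ratios and attributable risks; the effect on the PRS is smaller and conditional

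*Protocol article*

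**What the plan says.** Under Eligibility criteria, the protocol article draws controls from two sources. Hospital controls are all adults "seeking medical care for non-ASCVD conditions will be screened and enrolled during hospitalization". Community controls are described thus: "healthy individuals with no clinical complain will also be screened and enrolled at the same community". The split between the two is not given. The stated bar is the same for both groups: "Exclusion criteria for both cases and controls are previously known ASCVD". Balancing covers two variables only: "Cases and controls will be recruited in a 1:1 ratio adjusted for sex and age".

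The Variables section lists what will be related to case status: "traditional risk factors (smoking, diabetes, hypertension, obesity, anxiety and depression, unhealthy diet, physical inactivity, alcohol consumption, and apolipoprotein B/A1 ratio", together with demographic variables and the PRS. For variables with a significant OR, an "attributable risk estimate will be calculated for the genetic component (PRS) and other covariables".

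Under Data analysis, covariates enter the multiple model only if their univariate p-value is below 0.20, and backward elimination follows; the investigator may force in confounders. The Bias control section relies on strict adherence to the eligibility criteria to limit selection bias.

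**The concern.** Controls should show how common each exposure is in the population that produced the cases. Patients who are in hospital because of an exposure show it more often than that population does. The article sets an open rule with one exclusion, so admissions for a diabetic complication, a hypertensive crisis, smoking-related lung disease or alcohol-related illness all qualify.

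None of the stated safeguards reaches this. Strict adherence cannot remove a bias that the criteria themselves create. Balancing on sex and age does not address the reason for admission. Adjusting for the other factors leaves the affected factor's own OR distorted.

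Two analysis rules can make it worse. A factor whose OR is pulled toward 1 may fail the p < 0.20 screen or be eliminated, and a factor without a significant OR receives no attributable risk. Attributable fractions are the study's declared aim in the Introduction and Discussion, with the genetic component first and the modifiable factors alongside.

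**Working it through.** **The plan's own figure.** Inputs from Sample size calculation: OR 1.3, allele frequency 10%, dominant model, prevalence 10%, power 90%, two-sided 0.05.
- Carrier frequency = 1 − 0.9² = 0.19.
- Solving a logistic penetrance model for 10% prevalence gives carrier proportions of 22.87% in cases and 18.57% in controls.
- The two-proportion formula gives 1,868 per group, and a likelihood-ratio calculation gives 1,867. The stated 1,867 + 1,867 is reproduced, and this point does not alter it.

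The documents give no figure for contamination, so every contamination input below, and every exposure prevalence and risk-factor OR, is an assumption.

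**Modifiable factors.** Let p be the source prevalence, and let x be the share of all controls admitted for the exposure itself.
- Case odds = OR × p/(1 − p), which gives the case prevalence pc.
- Control prevalence = p(1 − x) + x.
- Observed OR = case odds / control odds.
- PAF = pc × (OR − 1)/OR.
- The OR equals 1 when x = (pc − p)/(1 − p).

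| Assumed factor | x | Control prevalence | Observed OR | PAF |
|---|---|---|---|---|
| Diabetes: p 10%, true OR 2.5, pc 21.7% | 0 | 10% | 2.50 | 13.0% |
| | 5% | 14.5% | 1.64 | 8.5% |
| | 10% | 19% | 1.18 | 3.4% |
| | 20% | 28% | 0.71 | – |
| Hypertension: p 30%, true OR 2.0, pc 46.2% | 0 | 30% | 2.00 | 23.1% |
| | 10% | 37% | 1.46 | 14.5% |
| | 20% | 44% | 1.09 | 3.8% |

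The OR reaches 1 at x = (0.217 − 0.10)/0.90 = 13% for diabetes and at x = (0.462 − 0.30)/0.70 = 23% for hypertension.

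**Does adjustment help?** A simulation used a 19% carrier frequency, a true adjusted genetic OR of 1.3, a diabetes OR of 2.5, and an allele that also raises diabetes (OR 1.3). Diabetic controls were then oversampled.

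| Oversampling of diabetic controls | Adjusted genetic OR | Adjusted diabetes OR |
|---|---|---|
| None | 1.30 | 2.49 |
| ×2 | 1.31 | 1.27 |
| ×3 | 1.30 | 0.83 |
| ×5 | 1.31 | 0.50 |

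The diabetes OR is in effect divided by the oversampling factor (2.5/2 = 1.25, 2.5/3 = 0.83, 2.5/5 = 0.50). The genetic OR is protected as long as diabetes stays in the model.

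**Genetic marker without that protection.** The marker of the sample size calculation stands in for the PRS. Half the controls are assumed to be inpatients, with an allele–diagnosis OR of 1.1 to 1.5.
- If 25% of inpatients have a related diagnosis: OR 1.28 to 1.23, PAF 5.1% to 4.3%, power 87% to 73%.
- If 50% do: OR 1.27 to 1.16, PAF 4.8% to 3.2%, power 84% to 48%.
- The uncontaminated values are OR 1.30, PAF 5.3% and power 90%.

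**The community controls.** If healthy volunteers had carrier odds 0.9 or 0.8 times those of the population and made up all the controls, the genetic OR would be 1.30/0.9 = 1.44 or 1.30/0.8 = 1.63. In mixtures with 25% to 75% hospital controls (25% or 50% of inpatients related, allele–diagnosis OR 1.3 or 1.5, healthy carrier odds 0.9 or 0.95), the net OR ran from 1.20 to 1.38, on both sides of 1.30.

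**The case against.** **The PRS is the main target and is largely protected.** A reader might infer that the PRS OR could also vanish or reverse. The documents do not support that. The stated aim is the genetic contribution after adjustment for modifiable factors, and the simulation keeps the adjusted genetic OR at about 1.30. In the unprotected calculation it fell below 1 only when every inpatient control had a related diagnosis with an allele OR of 1.5 and at least 75% of controls were inpatients. What remains is attenuation. The Discussion describes coronary loci "whose mechanism of action is related to serum levels of LDL-cholesterol, lipoprotein (a) and triglycerides, blood pressure, obesity", as well as coagulation and immune routes. Several of these, such as lipoprotein(a), triglycerides and coagulation, are not covariates in the Variables section. Covariates can also be eliminated, and univariate ORs are planned too. That review of loci is not a description of this study's own PRS, so the link stays conditional.

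**The bias need not run one way.** A reader might infer that all ORs and PARs are understated. The healthy community controls can push the other way, and with no stated split the net direction cannot be known. This stands. But two opposing biases in an unknown mix do not amount to a correction.

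**The full protocol is not shown.** The supplementary files may restrict admission diagnoses, and the Study organization section says that controls are adjudicated. That is possible. However, the article states an open rule with one exclusion, and nothing in it says that adjudication screens the reason for admission. If a restriction exists, the sponsor need only state it.

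**Conclusion.** The concern holds for the modifiable risk factors. As printed, the control definition admits patients hospitalised because of an exposure under study, and this can bias that factor's OR and PAR toward the null or, under heavy contamination, past it. Adjustment does not repair the factor's own OR, and the screening and significance rules may remove the factor or leave it without a PAR.

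On the assumed inputs, 5% of all controls admitted for diabetes takes an OR of 2.5 to 1.64 and its PAF from 13.0% to 8.5%; the null is reached at 13%. For the PRS, the supportable statement is possible attenuation through unmodelled pathways or dropped covariates. The net direction over both control sources is unknown. The actual size depends on the case mix of admissions and on the hospital/community split, neither of which the article gives.

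**What to change.** **Remaining recruitment.** Limit hospital controls to a spread of admission diagnoses unrelated to the studied exposures. Exclude by reason for admission and not by history of the exposure: a diabetic patient admitted for an unrelated reason stays eligible, because removing such patients would make the controls too healthy.

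**Controls already enrolled.** Classify the reason for admission, for example at the existing adjudication of controls, and retrieve it where it was not recorded. Estimate each factor's OR and PAR without controls admitted for a condition related to that factor. Show the all-controls result alongside, and results by control source, since removing inpatients shifts the remaining series toward healthy volunteers.

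**Cost.** An eligibility amendment, a coding step and some precision. The planned sample size need not change, but the loss should not be taken as negligible. Take all 1,867 cases and the plan's genetic OR of 1.3. Removing 30% of controls leaves 0.7 × 1,867 = 1,307 and power of about 84%. Removing 50% leaves about 934 and power of about 75%. Removal should therefore be factor-specific and not across the board, and the resulting precision should be reported.

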### Sample size calculation

We applied the following statistical assumptions: odds ratio for genetics was set at 1.3, allele frequency of 10%, inheritance model was dominant (since the presence of only one polymorphic allele is required to the risk calculation), the prevalence of CVD in the general population of 10%, statistical power of 90%, type I error rate (α) of 0.05, 2-sided significance tests, resulting in a sample of 1,867 cases and 1,867 controls. Sample size calculation was performed using Quanto Software Version 1.2.4.

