#### Bias control

Eligibility criteria for cases and controls will be strictly followed to reduce selection bias. The criteria defined for the first ASCVD event were standardized, and all sites have been trained for the correct identification, data recording, and reporting of information. Cases will be validated by the adjudication committee through clinical data, diagnostic tests, hospitalization and/or discharge summary, among others, using the standardized and validated process for diagnoses [45, 46]. The relationship between the variables will be adjusted by multivariate logistic models. Data monitoring will be applied throughout the entire study timeline to assure data quality. Blood and urine samples collection have been standardized, and genetic and biochemistry analyses will be performed in a core lab to guarantee the standardization of methods and quality control.

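### Inpatients and symptom-free community members form one control group, so the modifiable risk-factor ORs and PARs depend on the hospital/community mix as well as on the source population

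*Protocol article*

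**What the plan says.** Under Eligibility criteria, controls come from two sources. The first is adults "seeking medical care for non-ASCVD conditions will be screened and enrolled during hospitalization". The second is described thus: "healthy individuals with no clinical complain will also be screened and enrolled at the same community". The listed exclusions concern previously known ASCVD only, so nothing in that section keeps out an inpatient admitted for a condition caused by smoking, diabetes, hypertension or alcohol.

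The only ratio given is between cases and controls: "Cases and controls will be recruited in a 1:1 ratio adjusted for sex and age". Sample size calculation gives one undivided control total, "resulting in a sample of 1,867 cases and 1,867 controls".

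Variables, and Quantitative variables and statistical analysis, describe unconditional logistic regression of case versus control status. Attributable risk is then calculated for the PRS and for the other covariables that have a significant OR. Neither section distinguishes control types.

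On selection bias, Bias control states: "Eligibility criteria for cases and controls will be strictly followed to reduce selection bias". The limitations in the Discussion do not mention the two control sources.

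**The concern.** A PAR estimated from a case-control study needs controls whose exposure reflects the population that gave rise to the cases. Inpatients tend to over-represent smoking, diabetes, hypertension, obesity and alcohol use, because these also lead to other admissions. People chosen for having no complaint tend to under-represent them. The pooled control prevalence is then a weighted average of the two, and the article does not say what sets the weight across the 50 centers.

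Adjusting for sex, age and the other risk factors does not undo selection that acts on the factor being estimated. Strict adherence to the criteria does not help either, because the criteria themselves create the mixture.

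At stake are the ORs and PARs of the modifiable factors. The Discussion sets the genetic contribution against these. Covariates are screened at univariate p < 0.20 and then eliminated backward, and a PAR is calculated only for variables with a significant OR. The mix could therefore also influence which factors are kept and which receive a PAR.

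**Working it through.** **1. The plan's own figure.** Inputs from Sample size calculation: "odds ratio for genetics was set at 1.3"; "allele frequency of 10%, inheritance model was dominant"; CVD prevalence 10%; power 90%; two-sided α 0.05.
- Carrier frequency in the population: 1 − 0.9² = 0.19.
- A logistic penetrance model solved for 10% prevalence gives carrier frequencies of 0.2287 in cases and 0.1857 in controls.
- The unmatched 1:1 likelihood-ratio calculation gives 1,866.7, so 1,867 per group. The two-proportion formula gives 1,868, and power at 1,867 per group is 0.900.

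The stated size reproduces. It treats controls as one disease-free group and makes no provision for two control types.

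**2. Effect of the mix on a modifiable factor.** The document gives no exposure prevalence by control type, so the inputs here are assumptions. With exposure p₁ in cases, hospital share w, and p₀ = w·p_hosp + (1 − w)·p_comm:

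OR = [p₁/(1 − p₁)] / [p₀/(1 − p₀)]; PAR = p₁(1 − 1/OR).

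Scenario A, smoking: cases 35%, community 20%, hospital 28% (case odds 0.35/0.65 = 0.538).

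| Hospital share | p₀ | Control odds | OR | PAR |
|---|---|---|---|---|
| 0% | 0.20 | 0.250 | 2.15 | 18.75% |
| 50% | 0.24 | 0.316 | 1.71 | 14.5% |
| 100% | 0.28 | 0.389 | 1.38 | 9.7% |

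Scenario B, a commoner factor: cases 60%, community 30%, hospital 50%.

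| Hospital share | p₀ | OR | PAR |
|---|---|---|---|
| 0% | 0.30 | 3.50 | 42.9% |
| 25% | 0.35 | 2.79 | 38.5% |
| 50% | 0.40 | 2.25 | 33.3% |
| 75% | 0.45 | 1.83 | 27.3% |
| 100% | 0.50 | 1.50 | 20.0% |

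If the true source prevalence in B were 40%, the half-and-half pool would give the right answer (OR 2.25, PAR 33.3%), and either source alone would not. If prevalence is equal in the two control types, the mix has no effect.

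In this crude setting the ratio of the two source-specific ORs equals the exposure odds in hospital controls divided by those in community controls. In A it is 2.154/1.385 = 0.389/0.250 = 1.56. The study can therefore estimate the discrepancy from its own controls.

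**3. Effect on the genetic estimate.** Keep 0.2287 in cases and assume that control carrier frequency differs slightly by type, from 0.185 to 0.190. The OR moves from 1.31 to 1.26 and the PAR from 5.4% to 4.8%. This shift is also an assumption.

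**4. Precision of source-specific estimates.** With an equal split (934 of 1,867), and the exposure variance taken as the same in every group, the standard-error ratio is √[(1/1867 + 1/934) / (2/1867)] = 1.22.

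**The case against.** The article condenses a full protocol (S2 File, not shown). A quota by control type, excluded admission diagnoses or an analysis by source may be set there or in an analysis plan. That stands for the quota, and the absence of a stated mix is not itself the point. The article does positively state two unlike sources, one control total and one binary model. A quota alone would not resolve the matter, because a fixed blend still gives the PAR for that blend.

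A reader might infer that the estimates no longer reflect the source population at all. The document does not support this. The healthy controls come from the same community, and the mix matters only where exposure differs by control type.

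A reader might also infer that the main genetic result is compromised. The stated aim is the genetic attributable fraction after adjustment for the modifiable factors. If control type selects on those factors and they are in the model, the conditional PRS OR is largely protected. So is a PAR built from that OR and the exposure in cases.

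Finally, one might take community controls as the reference, or pool only if the two sources agree. Neither is secure. People selected as healthy are plausibly biased low, and in Scenario B the community-only analysis is further from the assumed truth than the half-and-half pool. A preliminary agreement test would make the final estimator depend on a test whose power is unknown.

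It is also fair that all prevalences above are assumed and that the figures are crude, while the plan reports adjusted ORs.

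**Conclusion.** The point holds for the ORs and PARs of the modifiable risk factors. As written, they depend on the hospital/community mix as well as on the source population wherever exposure differs by control type, and none of the described bias controls addresses this. The document does not allow the size or direction to be computed. Under the assumed prevalences, the crude PAR ranges from 18.75% down to 9.7% in Scenario A and from 42.9% down to 20.0% in Scenario B across the full range of hospital share. The PRS OR and genetic PAR should be much less affected. The sample size of 1,867 per group is not in question. This is a design weakness that can be made visible cheaply in the analysis. It is not an arithmetic error and does not invalidate the study.

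**What to change.** Keep the pooled analysis and prespecify two additions.

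1. Report ORs and PARs separately against hospital controls and against community controls, with an estimate and confidence interval for their difference (for example, the ratio of the two ORs). Read the two as a range, without treating either source as the unbiased reference.
2. For each modifiable risk-factor PAR, add a sensitivity analysis that leaves out hospital controls admitted for conditions caused by that factor.

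Both need control source and reason for admission to be recorded in the eCRF. Data source and measurement names neither. That list may not be exhaustive, since smoking and diet are analysed but not listed there either, so the sponsor should confirm this. Recruitment began in July 2022, so missing items might have to be recovered from site records.

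If the items are recorded, the cost is analysis wording plus less precise source-specific results: standard errors about 22% larger with an equal split, and larger still for the smaller source if the split is uneven.
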